# Treatment of Atopic Dermatitis Using a Full-Body Blue Light Device (AD-Blue): Protocol of a Randomized Controlled Trial

**DOI:** 10.2196/11911

**Published:** 2019-01-08

**Keywords:** atopic dermatitis, atopic eczema, blue light, irradiation, ultraviolet light

## Abstract

**Background:**

Irradiation with visible blue light (wavelength 400-495 nm) is a promising, effective, and safe new treatment option for chronic inflammatory skin diseases such as psoriasis and atopic dermatitis.

**Objective:**

We will perform a multicenter, placebo-controlled, double-blinded, 3-armed, prospective, randomized controlled trial to investigate the efficacy and safety of full-body blue light devices (wavelengths: 415 nm and 450 nm) compared with that of placebo irradiation for the treatment of atopic dermatitis.

**Methods:**

We are planning to enroll a total of 150 patients at the University hospitals in Göttingen (Germany), Marburg (Germany), and Geneva (Switzerland).

**Results:**

The trial was approved by the lead ethics committee of the medical faculty of the University of Göttingen (21/11/16). Further approvals were obtained from local and federal authorities (ethics committee Marburg, Cantonal Commission for Research Ethics Geneva, Suisse Medic, and Bundesinstitut für Arzneimittel und Medizinprodukte).

**Conclusions:**

We will disseminate the results in a peer-reviewed journal.

**Trial Registration:**

ClinicalTrials.gov NCT03085303; https://clinicaltrials.gov/ct2/show/NCT03085303 (Archived by WebCite at http://www.webcitation.org/73ucqkkA1)

**International Registered Report Identifier (IRRID):**

DERR1-10.2196/11911

## Introduction

### Background

Atopic dermatitis is a common chronic inflammatory disease of the skin with a lifetime prevalence of 10%-20% in adults in developed countries [1]. Mutations in the filaggrin gene were shown to play a key role in the etiology of the disease [2]. Patients present with itchy, red, dry or oozing lesions primarily at flexural body areas. Disease severity can be measured using the Eczema Area and Severity Index (EASI), which assesses redness, thickness, scratching, and lichenification on a scale of 0 (none) to 3 (severe) for different body regions [3]. SCORing Atopic Dermatitis (SCORAD) and Patient Oriented-SCORing Atopic Dermatitis (PO-SCORAD) are instruments that additionally consider the subjective symptoms of pruritus and insomnia [4,5]. The Investigator’s Global Assessment (IGA) is a score to assess overall disease severity on a scale of 0 (clear) to 4 (severe) [6]. Disease-related impairment of quality of life can be measured using the Dermatology Life Quality Index (DLQI) [7].

As atopic dermatitis is a chronic disease with an unpredictable and often relapsing course, long-term control is necessary [8]. In clinical practice, a stepwise approach is used, starting with active agent-free lipid balancing creams, cortisone-containing topical agents, and conventional ultraviolet (UV) irradiation for mild to moderate disease forms. Immunosuppressive medication is employed in more severely affected patients. Cortisone- containing topical agents effectively reduce inflammation but may also cause infection and skin atrophy in long-term use [9]. Conventional UV irradiation bears the risk of developing skin cancer and promotes accelerated skin aging [8]. Recently, a new treatment modality, UV-free blue light irradiation (wavelengths between 400 and 495 nm), was found to effectively improve inflammatory skin diseases at a favorable risk profile [10-13].

### Preliminary Data With Blue Light

Clinical data on blue light in chronic inflammatory skin diseases are scarce. Psoriasis and eczema have been the exclusive indications for comprehensive clinical trials in the past. Regarding eczema, Keemss et al [11] reported on 21 patients with mild to moderate disease who were locally treated with blue light-emitting diode (LED) light (wavelength: 453 nm) for 30 minutes 3 times per week for 4 weeks. No adverse events (AEs) occurred. The local Eczema Severity Index, which rates erythema, infiltration, lichenification, and crusts on a scale of 0 to 3, decreased on average by 1.9 (SD 2.02) in treated areas compared with that by 1.3 (SD 2.24) in untreated areas. Becker et al [10] investigated the treatment of 36 patients with severe atopic dermatitis with a full-body blue (FBB) light irradiation device (wavelengths between 400 and 500 nm accounted for 66% of the emission spectrum of the light source). Treatment consisted of 1 cycle of consecutive, daily blue light irradiations over 5 days. Each side of the body was irradiated for 24 minutes. Cycles were repeated in case of disease exacerbation, triggered by the patient’s demand. The EASI score in the treated patients improved by 41% and 54% after 3 and 6 months, respectively. The following transitory mild AEs were reported: local redness, warmth, and itching of the skin.

Other smaller studies investigated the effect of blue light on patients with psoriasis. Pfaff et al [12] used a localized blue light device (wavelength: 453 nm) to treat 49 patients with mild psoriasis for 30 minutes daily or almost daily for 12 weeks with 4 weeks of follow-up. After 78-90 days, the Local Psoriasis Severity Index significantly decreased compared to an untreated area (mean 0.92 [SD 1.10]). No treatment-related AEs occurred. Weinstabl et al [13] reported on localized irradiation of 40 patients with mild to moderate psoriasis with blue light. Group 1 (n=20) received treatment at home with blue light (LED, emission maximum: 420 nm) for 15 minutes once daily for 4 weeks (2 weeks follow-up). Group 2 (n=20) received treatment with another blue light device (LED emission maximum: 453 nm). The contralateral control plaques remained untreated in both groups. In both groups, the Local Psoriasis Severity Index significantly decreased in treated areas compared with that in untreated areas. No severe AEs occurred. Slight transient hyperpigmentation was noted after 3 weeks in both groups (59% and 50%, respectively). However, an FBB light device has not been clinically tested outside the mentioned studies.

## Methods

### Study Design

AD-Blue trial is a multicenter, placebo-controlled, double- blinded, 3-armed, prospective, randomized controlled trial (European Database on Medical Devices #CIV-16-11-017565 and ClinicalTrials.gov NCT03085303). We designed the clinical study following the Standard Protocol Items: Recommendations for Interventional Trials guidelines (see Multimedia Appendix 1).

### Objectives

The primary objective is to estimate the efficacy of irradiation with blue light (415 nm and 450 nm) compared with placebo irradiation in adult patients with atopic dermatitis, determined using multiple clinical scores, such as EASI and SCORAD. Secondary objectives comprise the assessment of safety, tolerability, and satisfaction with irradiation with blue light as well as the time until treatment response under therapy and the duration of response after the last irradiation.

### Endpoints

The primary endpoint is to determine the change from baseline in EASI in a comparison between treatment arms and placebo arm at the end of treatment. Secondary endpoints include the change from baseline in SCORAD, PO-SCORAD, visual analog scale of itch, DLQI, and IGA scores; the proportion of patients achieving 50% reduction from baseline EASI score (response); the so far mentioned endpoints at follow-up; and time until treatment response. The following safety endpoints will be addressed: change from baseline in hyperpigmentation of treated skin exposed to blue light and control as well as AEs (serious and nonserious), adverse device events (serious and nonserious), and device deficiencies.

### Study Population

A total of 150 patients with atopic dermatitis will be recruited at 3 sites: Geneva, Marburg, and Göttingen. The recruitment will be independent of the severity of disease and is limited to 50.0% (75/150) at each site. A sample size of 50 patients per group will have 84% power to detect a mean effect size of 0.6.

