### Methodology

We will randomize 150 patients diagnosed with atopic dermatitis 1:1:1 to arm 1 (irradiation for 30 minutes at 415 nm wavelength), arm 2 (irradiation for 30 minutes at 450 nm wavelength), and arm 3 (irradiation for 30 minutes at low-dose, placebo). We will stratify randomization by study site and initial EASI score (assessed during screening visit) with permuted and variable block sizes. For each strata combination, a list of separate randomization sequences will be generated using SAS 9.3 (Cary, NC). Irradiation will be scheduled 3 times a week for 8 weeks. Participants will be followed up for 4 weeks after the last irradiation. Patients will be blinded by wearing tinted protective goggles that disenable the distinction of different wavelengths of light. Medical doctors will examine patients in rooms other than those equipped with the investigational medical devices. These examiners are blinded and are, therefore, not involved in the preparation and process of irradiation. If the safety of an enrolled patient is potentially jeopardized, the investigator can break the blinding of the treatment. According to the predefined study schedule, we will measure skin pigmentation with a mexameter; take photos and blood samples; measure blood pressure; and gather data on Fitzpatrick skin type, DLQI, itch on visual analog scale, SCORAD, IGA, EASI, and PO-SCORAD scores. Detailed information on assessments is depicted in the study schedule (Multimedia Appendix 2). If the EASI score increases by 50% or more compared to baseline after at least 4 weeks of treatment (earliest: day 28=visit 13), a rescue scheme can be applied that allows the use of topical steroids or antihistamines. The investigator will decide whether to prescribe these medications, in what doses, and for how long. The respective patient will not drop out, but the rescue medication as well as the day of rescue will be documented. The study database will be provided by the Universitätsmedizin Göttingen, Ressort Forschung und Lehre, Referat Klinisches Studien Management using secuTrial, which is a browser-based electronic data capture system compliant with Good Clinical Practice (audit trail, role-rights concept). The database will be accessible via the internet.

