### Statistical Considerations

The primary analysis will be performed based on the full analysis set following the intention-to-treat principle. Dropouts during first 4 weeks of treatment will be replaced. Patients missing more than 5 irradiation appointments in total until day 25 (inclusive) or more than 3 consecutive irradiation appointments until day 25 (inclusive) will be considered dropouts and will be replaced. Dropouts after day 25 of the study protocol will not be replaced and will be analyzed in the intention-to-treat population. Sensitivity analysis will be done on the per-protocol population. The difference between the end of treatment after 8 weeks and baseline in primary effectiveness endpoint EASI will be analyzed using pairwise 2-sample *t* tests between each of both active treatments against placebo. As sensitivity analysis, an analysis of covariance will be used with study site, gender, and the hand out of topical emollient as additional factors and the EASI baseline value, age, and Fitzpatrick skin type as covariates. Other continuous secondary endpoints will be analyzed analogously. The EASI response will be analyzed primarily using chi-square test and as a sensitivity analysis with logistic regression. Time until treatment response will be analyzed using Kaplan-Meier estimator and log-rank test. In a further sensitivity analysis, if both wavelengths show better effectiveness than placebo, a pooled comparison against placebo will be done to increase the sample size.

The two comparisons, namely, 415 nm versus placebo and 450 nm versus placebo will be evaluated equally. To address the multiplicity, a success will be declared if both comparisons are statistically significant at an alpha level of .05 or if one of these two is statistically significant with respect to half of alpha at .025.

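### The stated 84% power is that of a single t test at two-sided .05 and does not reflect the plan's own two-comparison success rule; with two-sided tests, a lone effective wavelength has about 76%

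*Protocol article*

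**What the plan says.** The sample size rests on one sentence in the protocol article's Study Population section: "A sample size of 50 patients per group will have 84% power to detect a mean effect size of 0.6". That sentence gives no alpha level, sidedness, number of comparisons or allowance for dropout.

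The Methodology section fixes the allocation: "We will randomize 150 patients diagnosed with atopic dermatitis 1:1:1 to arm 1", with the second wavelength and placebo as the other two arms.

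Statistical Considerations sets the analysis. The primary test is a two-sample t test on the change in EASI, "between each of both active treatments against placebo". On their standing: "The two comparisons, namely, 415 nm versus placebo and 450 nm versus placebo will be evaluated equally". The success rule has two branches. In the first, "a success will be declared if both comparisons are statistically significant at an alpha level of .05". The second branch covers a lone positive comparison, and the trial then succeeds "if one of these two is statistically significant with respect to half of alpha at .025". No sidedness is given here either.

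On losses, dropouts up to day 25 are replaced, but "Dropouts after day 25 of the study protocol will not be replaced"; they remain in the intention-to-treat analysis. Missing endpoint values are filled by single regression imputation. No late dropout rate is given.

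**The concern.** The power sentence and the success rule are both printed in this article, and they do not describe the same test. A power of 84% at 50 per group and an effect of 0.6 belongs to one comparison at the full .05 level. Under the rule, a wavelength is tested at .05 only when the other is also significant at .05; otherwise it must reach .025. A rule with a branch for one significant wavelength needs a power figure for that case, and the article gives none.

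At stake is how the trial is read. Someone who takes 84% as the chance of detecting an effective wavelength will overrate what a miss at .025 says when the other wavelength has failed. Under two-sided testing, power in that case is below 80%, not above it.

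**Working it through.** **Inputs.** From the article: n = 50 per arm, standardized effect d = 0.6 (SD = 1), two comparisons sharing one placebo arm, two-sample t tests, and the .05/.025 rule. Assumed: two-sided tests, because sidedness is not stated.

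**Step 1: reproduce the stated figure.** For two groups of n, the noncentrality is d / √(2/n) and the degrees of freedom are 2n − 2. Here 0.6 / √(2/50) = 0.6 / 0.2 = 3.0, with 98 degrees of freedom.

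| Level | Critical t | Power |
|---|---|---|
| two-sided .05 | 1.984 | 84.4% |
| one-sided .025 | 1.984 | 84.4% |
| two-sided .025 | 2.276 | 76.4% |
| one-sided .05 | 1.661 | 90.9% |

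The stated 84% is therefore correct arithmetic for a single test at two-sided .05. One-sided .025 is the same calculation.

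**Step 2: apply the success rule.** A wavelength is claimed if its p ≤ .025, or if both p-values are ≤ .05. This was simulated with 400,000 trials per scenario, 50 per arm, a shared placebo arm and two-sided p-values.

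| True effects | Given wavelength at 0.6 | At least one | Both |
|---|---|---|---|
| 0.6 and 0 | about 76% | about 76–77% | – |
| 0.6 and 0.3 | 78% | 78% | 30% |
| 0.6 and 0.6 | 82% | 90% | 75% |

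The first row is close to the exact 76.4% from step 1, because an inert wavelength seldom reaches .05 and so seldom opens the .05 branch. The range in that row depends on whether significance in the wrong direction is counted.

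**Step 3: late losses.** No rate is given, so this is an illustration. Suppose 10% of week-8 information is lost, leaving 50 × 0.9 = 45 informative patients per arm, and imputation adds no information. The noncentrality is 0.6 / √(2/45) = 2.846 with 88 degrees of freedom.

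- Single test: 80.4% at two-sided .05 and 71.4% at two-sided .025.
- Rule, one wavelength at 0.6 and the other at 0: 71%.
- Rule, both at 0.6: 78% each, 86% for at least one, 69% for both.

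**Step 4: size of the gap.** For a lone effective wavelength it is 84.4 − 76.4 = 8.0 percentage points. Reaching 84% at two-sided .025 would take an effect of about 0.66 at 50 per arm, or 60 per arm at an effect of 0.6.

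**The case against.** The strongest reply is that the stated arithmetic is right and that a journal article may leave alpha, sidedness and scenario to the full protocol. The first half stands: 84% reproduces. The second half does not dispose of the point, because the article itself prints both the success rule and a power figure that does not follow from it.

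Further objections stand and limit the point:

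- **Sidedness.** If the levels are one-sided, the .025 threshold itself gives 84.4%. The 76% depends on two-sided testing, which is the usual reading of a .05 level but is not stated.
- **Scenario.** One effective and one wholly inert wavelength is close to the least favourable case. If both work at 0.6, per-wavelength power is 82%, only about 2 points short, and the chance of declaring success is 90%, above the stated figure.
- **Losses.** Early dropouts are replaced, and 47 per arm would still give 82.1% for the single test at two-sided .05. The 10% loss is an illustration only.

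Three stronger readings are tempting, and the article supports none of them. A reader might infer that no scenario under the rule yields 84%. That is untrue: the chance of at least one success is about 83% to 85% when the second effect is 0.45 to 0.5, and a wavelength at 0.6 has about 84% when the other is at 0.8. A reader might infer that the 84% is the benchmark for the interim look, but the article says sufficiency will be judged from the interim estimates and does not mention the 84% there. A reader might expect baseline adjustment in the primary analysis to make up the shortfall. The primary analysis is an unadjusted t test on change; covariance analysis with baseline EASI is only a sensitivity analysis, and the correlation needed to size any gain is not given.

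**Conclusion.** The point holds in a conditional form. The 84% describes one comparison at two-sided .05 and is not tied to the rule by which the trial declares success. With two-sided tests, 50 per arm and an effect of 0.6, the shortfall is about 8 points for a lone effective wavelength and about 2 points per wavelength when both work, while power for at least one success is then about 6 points higher than stated (90%). Late losses would lower all of these by an amount the article does not allow one to fix.

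This is a mismatch between two stated elements. It is not a calculation error, and it does not show that the trial was too small for every outcome it could claim.

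**What to change.** Replace the unqualified sentence in Study Population with power under the stated rule, naming alpha, sidedness and scenario each time. If the tests are two-sided, 50 per arm and an effect of 0.6 give:

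- about 76% if only one wavelength works and the other has no effect;
- 82% for each wavelength, 90% for at least one and 75% for both, if both work at 0.6.

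Add one line for losses after day 25 under an explicit assumption. With 45 informative patients per arm, the figures are 71% for a lone effective wavelength, and 78% each, 86% for at least one and 69% for both if both work. If the levels were meant to be one-sided, say so and recompute.

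No extra patients and no change to the analysis are needed; enrolment was already complete in May 2018. The cost is a slightly less favourable stated figure.

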### Recruitment and Status of the Study

The first enrollment took place in March 2017. The study duration per patient is 13 weeks (1 week of screening, 8 weeks of irradiation, and 4 weeks of follow-up), and the estimated total time frame for recruitment of 150 patients is 14 months (last visit of the last patient estimated to be in August 2018). During July to September, no irradiations will take place due to the possible improvement of disease severity linked to the increased natural sun exposure.

### Inclusion and Exclusion Criteria

Patients aged 18-75 years with atopic dermatitis according to the UK criteria of atopic dermatitis [14] and a body mass index between 18 and 35 kg/m^2^ who are willing to abstain from excessive sun or UV exposure and have given written informed consent will be eligible. Patients with a severe past or present disease that may affect the outcome of the study, including HIV or hepatitis B or C; patients with a risk of noncompliance with study procedures; pregnant or nursing women; patients with alcohol or drug abuse within 12 months prior to screening; patients with photodermatosis, photosensitivity, immunodeficiency, or genetic deficiencies with increased sensitivity to light; and patients who have been diagnosed with invasive skin cancer at any time or with severe actinic damage present at baseline visit will be excluded from the trial.

We will prohibit the following concomitant medication within a certain timeframe before and during the study: systemic immunosuppression treatment such as glucocorticoids, cyclosporine, azathioprine, and mycophenolate mofetil (within 8 weeks prior to baseline visit); UV irradiation treatment (within 4 weeks prior to baseline visit); topical steroids or calcineurin inhibitors (within 2 weeks prior to baseline visit); and photosensitizing medication and colors on the patient’s skin (within 3 days prior to baseline visit). Active agent-free lipid balancing creams (Unguentum leniens) will be allowed during the trial and handed out on request.

### Investigational Devices

We will investigate FBB-CT01 devices (Philips; Aachen, Germany; not Conformité Européene, CE, marked) with LEDs emitting blue light (Figure 1). This will be done by using the following three different parameter settings:

415 nm device: Device equipped with 415 nm wavelength LEDs. Light output=40 mW/cm^2^. Light module equipped with fans.450 nm device: Device equipped with 450 nm wavelength LEDs. Light output=40 mW/cm^2^. Light module equipped with fans.Placebo device: Device equipped with 450 nm wavelength LEDs. Light output=0.2 mW/cm^2^. Light module without fans.

The devices are on lock wheels for easy transportation. We will administer phototherapeutic light for 15 minutes to each side of the body of the patient (30 minutes in total for both sides) who will lie flat on a treatment table. We will provide specific protective goggles to filter the blue color of the light. Once the user presses the ON button to switch on the device, all treatment LEDs will be on. If the user needs to stop the treatment, he or she will either press the OFF button or, in case of an emergency, the “emergency stop” button.

### Methodology

We will randomize 150 patients diagnosed with atopic dermatitis 1:1:1 to arm 1 (irradiation for 30 minutes at 415 nm wavelength), arm 2 (irradiation for 30 minutes at 450 nm wavelength), and arm 3 (irradiation for 30 minutes at low-dose, placebo). We will stratify randomization by study site and initial EASI score (assessed during screening visit) with permuted and variable block sizes. For each strata combination, a list of separate randomization sequences will be generated using SAS 9.3 (Cary, NC). Irradiation will be scheduled 3 times a week for 8 weeks. Participants will be followed up for 4 weeks after the last irradiation. Patients will be blinded by wearing tinted protective goggles that disenable the distinction of different wavelengths of light. Medical doctors will examine patients in rooms other than those equipped with the investigational medical devices. These examiners are blinded and are, therefore, not involved in the preparation and process of irradiation. If the safety of an enrolled patient is potentially jeopardized, the investigator can break the blinding of the treatment. According to the predefined study schedule, we will measure skin pigmentation with a mexameter; take photos and blood samples; measure blood pressure; and gather data on Fitzpatrick skin type, DLQI, itch on visual analog scale, SCORAD, IGA, EASI, and PO-SCORAD scores. Detailed information on assessments is depicted in the study schedule (Multimedia Appendix 2). If the EASI score increases by 50% or more compared to baseline after at least 4 weeks of treatment (earliest: day 28=visit 13), a rescue scheme can be applied that allows the use of topical steroids or antihistamines. The investigator will decide whether to prescribe these medications, in what doses, and for how long. The respective patient will not drop out, but the rescue medication as well as the day of rescue will be documented. The study database will be provided by the Universitätsmedizin Göttingen, Ressort Forschung und Lehre, Referat Klinisches Studien Management using secuTrial, which is a browser-based electronic data capture system compliant with Good Clinical Practice (audit trail, role-rights concept). The database will be accessible via the internet.

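### As written, an EASI halved after rescue medication counts as treatment response, which favors whichever arm is rescued more; the response endpoints need a rescue rule

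*Protocol article*

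**What the plan says.** The rescue rule is in the protocol article, Methodology. Its trigger reads: "If the EASI score increases by 50% or more compared to baseline after at least 4 weeks of treatment (earliest: day 28=visit 13". In that case "a rescue scheme can be applied that allows the use of topical steroids or antihistamines", with use, dose and duration left to the investigator. The section continues: "The respective patient will not drop out, but the rescue medication as well as the day of rescue will be documented".

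Endpoints lists among the secondary endpoints "the proportion of patients achieving 50% reduction from baseline EASI score (response", with no condition on rescue, and then "the so far mentioned endpoints at follow-up; and time until treatment response". Objectives describes the time endpoint as "the time until treatment response under therapy".

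Statistical Considerations bases the primary analysis on the full analysis set under intention to treat. For response it states: "The EASI response will be analyzed primarily using chi-square test", with logistic regression as a sensitivity analysis. Time to response is analyzed by Kaplan-Meier and log-rank. Only missing values are imputed. The day of rescue appears in none of these analyses, neither as a condition nor as a covariate.

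Inclusion and Exclusion Criteria lists topical steroids among the medication prohibited before and during the study. Of cortisone-containing preparations, Background says that "topical agents effectively reduce inflammation".

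**The concern.** A rescued patient has, by the trigger, clearly worsened under the allocated irradiation. If that patient is then given a drug that the article itself calls effective and the EASI falls to half of baseline, the stated rules record a success of the allocated arm. For an endpoint named response, and for a time described as being under therapy, that credits the light, or the placebo light, with what rescue may have done.

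The error need not cancel between arms. Rescue follows from worsening, so the arm that works less well can be expected to have more of it and to collect more of these borrowed responses. At stake are the EASI-50 comparison at the end of treatment and at follow-up, and the log-rank comparison of time to response. All are secondary endpoints.

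**Working it through.** **1. The plan's own figure.** Study Population gives 84% power for 50 per group and an effect size of 0.6. With a two-sample *t* test the noncentrality is 0.6 × √(50/2) = 3.0 on 98 degrees of freedom. At two-sided .05 (sidedness is not stated, so two-sided is assumed) power is 84.4%; the normal approximation gives 85.1%. The figure reproduces. It concerns the primary EASI change and is not affected by this point. The article gives no response rate, no rescue rate and no power for EASI-50.

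**2. One patient through the rules.**
- Baseline EASI = B. The rescue trigger is at least 1.5 B, on day 28 or later.
- The patient stays in the trial (Methodology) and in the intention-to-treat set (Statistical Considerations).
- The later EASI is observed, not missing, so imputation does not touch it.
- If it is 0.5 B or lower, the definition in Endpoints is met.
- The fall needed from the trigger is 1 − 0.5/1.5 = 67%.

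With 8 weeks of treatment and 4 of follow-up, rescue can start about 4 weeks before the end-of-treatment assessment and about 8 weeks before the end of follow-up.

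**3. Effect on the response difference.** Let p be the response rate with rescue counted as non-response, r the proportion rescued, and q the chance of EASI-50 after rescue, taken as equal in both arms. Then

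observed rate = p + r × q

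observed difference = (p_active − p_placebo) + (r_active − r_placebo) × q

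The sign of the bias is therefore the sign of r_active − r_placebo.

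**4. Illustration.** All rates are assumed: p = 45% active and 20% placebo, a 25-point difference, with q from 10% to 50%. Power is for two proportions, 50 per arm, two-sided .05, normal approximation with pooled variance under the null. Without post-rescue responses: pooled rate 0.325, standard errors √(2 × 0.325 × 0.675/50) = 0.0937 under the null and √((0.45 × 0.55 + 0.20 × 0.80)/50) = 0.0903 under the alternative, so z = (0.25 − 1.96 × 0.0937)/0.0903 = 0.73 and power is 77%.

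| Rescue active / placebo | Shift in difference, q = 10% to 50% | Observed difference | Power |
|---|---|---|---|
| 2% / 10% | −0.8 to −4.0 points | 24.2 to 21.0 | 74% to 60% |
| 5% / 20% | −1.5 to −7.5 points | 23.5 to 17.5 | 71% to 43% |
| 10% / 10% | 0 | 25.0 | 76% to 74% |
| 20% / 5% | +1.5 to +7.5 points | 26.5 to 32.5 | 81% to 93% |

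For example, in the second row with q = 50%, active is 45 + 5 × 0.5 = 47.5% and placebo is 20 + 20 × 0.5 = 30%, a difference of 17.5 points. The lost 7.5 points correspond to 0.075 × 50 = 3.75 patients in an arm of 50.

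Time to response was not quantified. Post-rescue events enter it by the same route, from day 28 on.

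**The case against.** The strongest objection is that the article is silent rather than wrong. No section says that post-rescue values count as response, and none excludes them. Handling of rescue is ordinary content of an analysis plan, which is not shown, and the recorded day of rescue would allow exactly the rule proposed here. The words on response under therapy may even have been meant to restrict response to irradiation. This stands in part: an unseen plan may already settle the matter. But the article does fix the endpoint definition, the retention of rescued patients, the analysis set, the tests and which values are replaced. Applied together, these count a post-rescue response.

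A second objection is that the per-protocol sensitivity analysis may remove rescued patients, since topical steroids are on the prohibited list. The article does not say so, and if it did, the analysis would selectively remove treatment failures.

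A third is that including post-rescue values regardless of rescue is a legitimate strategy. For EASI change under intention to treat it is. A reader might infer that the primary comparison also loses power, by subtracting a rescue effect from 0.6. The documents do not support that: they do not say that 0.6 is a rescue-free effect, so the subtraction could double count.

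A fourth concerns size. The assumed rates have no source in the article. A fall of about 67% is demanding, rescue is discretionary and starts no earlier than day 28, and it may consist of antihistamines only. This stands: the 50% post-rescue success behind the largest losses is an upper illustration, and at 10% the loss is 0.8 to 1.5 points.

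**Conclusion.** The point holds for EASI-50 response and time to response. The stated rules let improvement after rescue count as response to the allocated irradiation, and that does not fit the stated objective.

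A reader might infer that the bias always works against blue light. It does so only if placebo is rescued more. That is plausible if blue light works, but the article gives no rescue rates. With equal rescue the difference is unchanged, and with more rescue on an active arm it is inflated, so a poorly performing arm could look better than it is.

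The size is unknown. Under the assumed rates with more rescue on placebo, a 25-point difference falls by about 1 to 7.5 points; with more rescue on active it grows by 1.5 to 7.5 points. These figures rest on assumed response and rescue rates and on equal post-rescue success in both arms. The primary endpoint and its stated 84% power are not called into question.

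**What to change.** In Statistical Considerations, add:

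1. For EASI-50, a patient is a non-responder at every visit after the documented day of rescue.
2. For time to response, a patient rescued before responding stays in the risk set as not responded to the end of observation. Do not censor at rescue: rescue is triggered by worsening, so such censoring would be informative.
3. Keep the observed-value analysis of EASI change as primary, and report the observed-value analysis of EASI-50 as a companion. Optionally, add a sensitivity analysis of EASI change that handles post-rescue values, noting that carrying forward the pre-rescue value penalizes the arm with more rescue.

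If the analysis plan already contains such a rule, it is enough to cite it.

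The clinical rescue rule is not changed. Inclusion and Exclusion Criteria (topical steroids prohibited during the study) and Methodology (topical steroids possible as rescue) contradict each other as worded and must be reconciled.

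The Results section says that data analysis is under way. The rule should therefore be recorded before unblinded results are seen, or else be labeled post hoc.

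The cost is small: the day of rescue is already recorded. The downside is slightly lower response rates and a little more analysis work.
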